#### Study 2 Relationship between social cognition and risk-taking behaviour (ecological validity).

The relationship between SC test performance and actual social behaviour (ecological validity), specifically risk-taking behaviour, will be investigated by analysing the relationship between the SC tests and the risk-taking measures with parametric or non-parametric correlation analyses in the different groups (bvYOD, non-bvYOD, brain injury, healthy controls). A significant correlation will demonstrate an association between social cognition and risk-taking behaviour and therefore, be indicative ecological validity. By looking specifically at the association between SC and risk-taking behaviour in patients with frontal brain injury, it will be assessed whether this relationship is generic for all patient groups with SC impairments. Furthermore, by assessing this relationship specifically in patients with non-bvYOD, for whom no SC impairments or risk-taking behaviour are expected, it will be assessed whether this relationship is specific.

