**Methods:**

The YOD-RiSoCo study is an observational prospective cohort study, consisting of two separate, but related, studies. Study 1 includes 64 patients with bvYOD and 64 healthy controls to assess the sensitivity and validity of newly developed SC instruments for measuring emotion experience and empathy, by comparing their average group performance. Furthermore, validity of the new instruments will be assessed by analysing the associations of performances on these new tests with those on more traditional SC and other neurocognitive tests. Study 2 focuses on assessing to which extent SC measures relate to risk-taking behaviour. This study includes 20 patients with bvYOD and 20 healthy controls from Study 1, in addition to 20 patients with non-bvYOD (e.g. Alzheimer’s dementia or vascular dementia) and 20 patients with serious brain injury affecting frontal networks. A specific question is whether the relationship between SC and risk-taking behaviour is generic (for all groups with SC impairments), or specific (not in dementia without SC impairments).

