## Methods and materials

### Study design study 1

Study 1 of the YOD-RiSoCo study is an observational prospective cohort study, that aims to include 64 patients with bvYOD and 64 healthy controls. Controls will be matched to patients on a group level, so that sex, age, and educational level distributions do not significantly differ between groups. The recruitment of controls will be adapted to match the included patients.

### Study design study 2

Study 2 of the YOD-RiSoCo study is an observational study that aims to include 20 patients with bvYOD, 20 healthy controls, 20 non-bvYOD patients and 20 patients with brain injury affecting frontal processes. The bvYOD and healthy control patients will be included from Study 1 (Fig 1).

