### Statistical analysis

The analyses will be conducted in Statistical Package for the Social Sciences (SPSS). Assumptions for the intended analyses will be checked. Parametric tests will be used for normally distributed data, otherwise a non-parametric alternative will be used. For all analyses, the alpha will be set at 0.05, and analyses will be two-sided. In case of multiple comparisons, Bonferroni-Holm correction, or another appropriate correction, will be applied. Demographic variables will be analysed on a descriptive level (mean, standard deviation, frequency, percentage). To ensure matched groups of patients and controls, comparisons will be made on demographic variables with t-test (or non-parametric tests such as chi-square or Mann-Whitney U tests). Potential confounders will be included as covariates.

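### Study 2 plans to judge whether the link between social cognition and risk-taking is generic or specific from separate correlations in groups of 20, with no comparison between groups

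*Protocol article*

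**What the plan says.** The third main aim, at the end of the Background, is to assess the relationship between SC and unsafe risk-taking and to find out whether it is generic or specific. The abstract (Methods) words the question as whether the relationship is "generic (for all groups with SC impairments), or specific (not in dementia without SC impairments"). The Study design section for Study 2 says that it "aims to include 20 patients with bvYOD, 20 healthy controls, 20 non-bvYOD patients and 20 patients with brain injury affecting frontal processes".

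The analysis section for Study 2 plans "parametric or non-parametric correlation analyses in the different groups (bvYOD, non-bvYOD, brain injury, healthy controls"). Its criterion is: "A significant correlation will demonstrate an association between social cognition and risk-taking behaviour". It then turns to the brain-injury group, where "it will be assessed whether this relationship is generic for all patient groups with SC impairments", and after that to the non-bvYOD group to judge whether the relationship is specific. The general Statistical analysis section adds: "For all analyses, the alpha will be set at 0.05, and analyses will be two-sided", and: "In case of multiple comparisons, Bonferroni-Holm correction, or another appropriate correction, will be applied". It also provides for covariates. No interaction term, slope comparison or test between correlations appears anywhere. The only sample-size calculation is for the Study 1 group difference.

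**The concern.** A relationship is specific, in the abstract's sense, if it exists where SC is impaired and is absent in dementia without SC impairment. That is a statement about a difference between groups. The stated analysis yields one p-value per group and nothing on the difference. A significant result in one group beside a non-significant result in another does not show that the two relationships differ, and with 20 people a non-significant correlation is common even when a real one exists.

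At stake is the generic/specific part of the third aim. A reader could be told that the link is confined to some diagnoses when the data show only that one small group crossed the threshold and another did not.

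**Working it through.** **The plan's own figure.** The Sample size section gives 64 per group for an effect size of 0.5, 80% power and two-sided 5%. A two-sample t-test calculation gives 63.8, so 64, with power 0.801. The figure is reproduced, but it concerns Study 1 only; no calculation supports the 20 per group in Study 2.

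**Inputs.** From the article: n = 20 per group and two-sided alpha 0.05. Assumed: bivariate normal scores and a common true correlation rho in bvYOD and non-bvYOD. The article gives no expected correlation, so a range is shown.

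**Step 1, threshold.** With 18 degrees of freedom, t = 2.101, and the critical |r| = 2.101 / √(18 + 2.101²) = 0.444. An observed r of exactly 0 at n = 20 has a 95% CI of tanh(±1.96/√17), that is −0.44 to 0.44. A null result in one group therefore excludes little.

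**Step 2, false 'specific' pattern.** Let q be the power in one group (simulated). The groups are independent, so P(significant in bvYOD, not significant in non-bvYOD) = q(1 − q). If significance in brain injury is also required, with the same rho there, it is q²(1 − q).

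| Common rho | q | q(1 − q) | q²(1 − q) |
|---|---|---|---|
| 0.2 | 0.135 | 11.7% | 1.6% |
| 0.3 | 0.254 | 19.0% | 4.8% |
| 0.4 | 0.430 | 24.5% | 10.5% |
| 0.5 | 0.641 | 23.0% | 14.7% |
| 0.6 | 0.835 | 13.8% | 11.5% |
| 0.7 | 0.956 | 4.2% | 4.0% |

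The ceilings are algebraic: q(1 − q) cannot exceed 25% (at q = 1/2), and q²(1 − q) cannot exceed 4/27 = 14.8% (at q = 2/3). All figures are for one pair of SC and risk measures. The study has several of each, so the chance of at least one such pattern is higher, by an amount that depends on how the measures correlate.

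**Step 3, multiplicity correction.** The article does not define the family for these correlations. At 0.05/4 = 0.0125 (the first Holm step for an assumed family of four groups), q(1 − q) is 4.5%, 9.7%, 17.5%, 24.3%, 22.6% and 11.0% at rho 0.2 to 0.7. The peak moves to a larger rho and does not disappear.

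**Step 4, direct comparison.** Under the same equal-correlation scenarios, a test of the slope difference (the SC × group term) rejects in 5% of cases. A Fisher z comparison of the two correlations, with SE = √(2/17) = 0.343, rejects in about 5% too.

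**Step 5, power of the direct comparison.** For 0.5 versus 0, the Fisher z difference is 0.549, and 0.549/0.343 = 1.60. Power is about Φ(1.60 − 1.96) = 36%; a simulated slope interaction gives 39%. For 0.6 versus 0 the Fisher z power is 52%, and for 0.7 versus 0 it is 72%. For 80% power the Fisher z test needs about 56, 36 and 24 per group respectively.

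**The case against.** The strongest reply is that the article never says that significance in bvYOD with non-significance in non-bvYOD means 'specific'. It says only that the matter will be assessed, and its one criterion concerns association within a group. That stands: the rule is inferred from the abstract's definition together with the Study 2 analysis text. But the article does state its method and criterion, and it gives no other route to the verdict, so this is more than a detail left to a fuller document.

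The size of the error also needs care. A reader might infer a false-positive rate of one in four. That is a ceiling, reached only for a correlation of about 0.4 to 0.5. The rate is lower on either side, lower at smaller correlations once alpha is corrected, and at most about 15% if significance in brain injury is also required. Nor does it follow that a true generic relationship is usually missed. With equal correlations, bvYOD and brain injury are both significant in 41% of cases at 0.5 (0.641²), but in 70% at 0.6 and 91% at 0.7.

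A reader might also take the abstract's 'or' to make the two verdicts mutually exclusive, so that the expected pattern could not be reported. The Study 2 analysis text does not support this: it sets out two separate assessments, and both can be answered yes.

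Finally, the main outcome is the Study 1 group difference, and the data would allow a between-group test later. Both are true. They lower the severity but do not make the stated method adequate.

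**Conclusion.** The point holds as a should-fix. The stated analysis cannot support a claim that the relationship differs between groups. Read as it appears to be intended, it would produce a 'specific' pattern in about 4% to 25% of cases per pair of measures when the true correlation is the same in bvYOD and non-bvYOD, for correlations from 0.2 to 0.7. A direct slope comparison holds 5%. The range rests on assumed correlations, bivariate normality, 20 complete cases per group and the inferred decision rule. The conclusion that a between-group comparison is needed depends on none of these figures. The Study 1 main outcome and its sample size are not affected.

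**What to change.** Keep the within-group correlations as description, each with a 95% CI. Base the generic/specific conclusions on one regression per risk measure, with SC score, group and SC × group, and any covariates already foreseen. State two contrasts in advance:

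- **Specific:** non-bvYOD slope versus bvYOD slope. Claim 'specific' only if the CI of this contrast excludes zero.
- **Generic:** brain-injury slope versus bvYOD slope. Report the brain-injury slope and the contrast with CIs. Do not claim 'generic' from a non-significant difference alone.
- **Otherwise:** report 'not resolved'.

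Use a rank-based or bootstrap version if the assumptions fail, which keeps the non-parametric option in the article.

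Comparing slopes is safer here than comparing correlations. The article expects no SC impairment in non-bvYOD, so scores there may vary less, and a narrower range lowers a correlation even when the slope is the same. As an illustration, assume equal slopes, a correlation of 0.5 in bvYOD, and an SC standard deviation in non-bvYOD half that in bvYOD. The Fisher z comparison then rejects in 12.3% of cases and the slope test in 5.0%.

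Do not use a slope pooled over all three patient groups as the main evidence of association. Its power is about 86% if the correlation is 0.4 in every group, but about 52% at 0.4, 0.4 and 0, which is the pattern that 'specific' describes.

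The cost is one rewritten paragraph and one model that SPSS can fit, with no added patients or data. The price is candour about precision: with power of about 36% to 39% for 0.5 versus 0, 'not resolved' is a likely outcome. Recruitment is planned to run to the end of 2026, so the change can still be specified before analysis.

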
#### Study 2: Investigate relationship between social cognition and risk-taking behaviour (ecological validity).

To investigate the relationship between social cognition and risk-taking behaviour, new and existing social cognitive measures will be administered to participants. Furthermore, risk-taking behaviour will be assessed with the Action Selection Task (AST) from the Institute of Road Safety Research (SWOV), the newly developed Risk-Taking Survey, and the newly developed Risk-taking in Traffic Task (RiTT), see Table 2. To account for the influence of other cognitive aspects, all general cognitive measures from Study 1 will also be administered in Study 2.

**Table 2 pone.0324517.t002:** Assessment instruments Study 2 Association SC and risk-taking behaviour.

Assessment	Construct
Study 2 also includes all assessments that are conducted in Study 1	
Risk-taking in Traffic Task (RiTT) (new)	Risk-taking behaviour in a driving simulator task
Risk-taking survey (RTS) (new)	Risk-taking behaviour in daily life
Action Selection Task (AST)	Risk-taking behaviour in static traffic situations
Mirror Test	Mimicry

The Risk-taking survey measures the degree to which a person can accurately identify situations that contain a possible risk for themselves or for another person. It consists of 30 *Yes-No* questions to be completed by the participant after a standardized instruction by the examiner. The instruction is as follows: “Here you are provided with a list of behaviour of people. Is it in your opinion *dangerous* or *risky* to do these things? Please check yes or no. With regard to *risky*, think of something that has a considerable chance to have adverse consequences, immediately, or in the longer term, and what you, therefore, should better not do.” Examples of questions are *“Is it risky or dangerous to sit in the backseat of a car, without your seat belt fastened?”* (Yes), or *“Is it risky or dangerous to eat a pastry with whipped cream on a birthday, in the presence of young children?”* (No).

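### Study 2 asks whether the social cognition/risk-taking relationship differs between groups, but states only separate significance-tested correlations in groups of 20 and no between-group comparison

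*Protocol article*

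**What the plan says.** Study 2 has four equal groups; it "aims to include 20 patients with bvYOD, 20 healthy controls, 20 non-bvYOD patients and 20 patients with brain injury affecting frontal processes" (Study design study 2). The Abstract explains the two possible answers to aim 3. Generic means the relationship holds in all groups with SC impairments, and specific means it does not hold in dementia without them.

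The Study 2 part of Statistical analysis relates SC tests to risk-taking measures "with parametric or non-parametric correlation analyses in the different groups (bvYOD, non-bvYOD, brain injury, healthy controls"). The criterion follows: "A significant correlation will demonstrate an association between social cognition and risk-taking behaviour". From the brain-injury group "it will be assessed whether this relationship is generic for all patient groups with SC impairments". From the non-bvYOD group, "for whom no SC impairments or risk-taking behaviour are expected, it will be assessed whether this relationship is specific".

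The general paragraph of Statistical analysis sets a two-sided alpha of 0.05, a Bonferroni-Holm or other correction for multiple comparisons, and covariate adjustment for potential confounders. The article states no test comparing correlations or slopes between groups. The Sample size section covers only the Study 1 mean difference.

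**The concern.** Generic versus specific is a question about a difference between groups. Finding significance in one group and not in another does not test that difference. With 20 people per group, two groups with the same relationship can easily fall on opposite sides of the threshold.

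The design may also tilt the result. The non-bvYOD group is chosen because neither SC impairment nor risk-taking is expected in it. If SC scores vary less there, the correlation shrinks even when the slope is the same.

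Two errors are at stake. A shared relationship could be reported as specific to bvYOD, or a generic one could be missed. The Discussion says that if a relationship is found, fitness-to-drive guidance for bvYOD or brain injury should be reviewed and revised, so it matters which groups are said to show it.

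**Working it through.** **The plan's own figure.** The only sample size calculation is for Study 1: d = 0.5, 80% power, two-sided 5%. The noncentral t gives 63.8, so 64 per group, with power 0.801. This reproduces and is not in dispute. There is no corresponding figure for Study 2.

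**Inputs.** n = 20 per group (Study design study 2); two-sided alpha 0.05 (Statistical analysis). The true SC/risk-taking correlation ρ is not given, so I assume a range of 0.2 to 0.7. Pearson correlation and bivariate normal data are assumed.

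**Step 1: threshold in one group.** t(0.975, 18) = 2.101, so critical |r| = 2.101/√(18 + 2.101²) = 0.444. Power of 80% needs ρ of about 0.58.

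**Step 2: two groups with the same ρ.** With per-group power p (simulated), the chance that exactly one group is significant is 2p(1−p). The pattern that reads as specific (bvYOD significant, non-bvYOD not) is p(1−p). The chance that bvYOD and brain injury are both significant is p².

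| ρ | p | exactly one significant | reads as specific | both significant |
|---|---|---|---|---|
| 0.2 | 0.13 | 23% | 12% | 2% |
| 0.3 | 0.25 | 38% | 19% | 6% |
| 0.4 | 0.43 | 49% | 25% | 19% |
| 0.5 | 0.64 | 46% | 23% | 41% |
| 0.6 | 0.84 | 28% | 14% | 70% |
| 0.7 | 0.96 | 8% | 4% | 91% |

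So at ρ = 0.5 in both bvYOD and brain injury, a generic relationship fails to show in both groups 59% of the time.

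These figures use unadjusted alpha. The planned correction lowers p. With nine tests (an assumption, for illustration), first-step power at ρ = 0.5 is about 0.30.

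**Step 3: less spread in non-bvYOD.** Keep the slope and residual SD fixed and let u be the ratio of SC standard deviations. Then r′ = ρu/√(1 − ρ² + ρ²u²). No SDs are given, so u is an assumption. At ρ = 0.5, with p = 0.64 in bvYOD:

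| u | r′ | power in non-bvYOD | bvYOD significant, non-bvYOD not |
|---|---|---|---|
| 1 | 0.50 | 0.64 | 23% |
| 0.75 | 0.40 | 0.43 | 37% |
| 0.5 | 0.28 | 0.22 | 50% |

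There is no slope difference in any row.

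**Step 4: what a null can show.** At r = 0 and n = 20 the Fisher limits are ±1.96/√17 = ±0.475, which back-transform to about −0.44 to 0.44.

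**Step 5: what a direct comparison can show.** For 20 v 20, the SE of the Fisher z difference is √(1/17 + 1/17) = 0.343. At 80% power the detectable difference is 2.80 × 0.343 = 0.96, that is, about r = 0.74 v 0. Power is 36% for 0.5 v 0 and 52% for 0.6 v 0. The false-difference rate is held at about 5%.

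**The case against.** The strongest reply is that the article never says that significance in bvYOD with non-significance in non-bvYOD will be declared specificity; it says only that the question will be assessed. That is correct, and a reader should not take the rule as plan text. It is an inference from the significance criterion, the group-by-group correlations and the Abstract's definition. The article gives no other basis, however. An analysis plan that is not shown might add a comparison, but one that only followed the article would inherit the gap.

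Three other points limit the finding:

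- **Size.** The figures depend on an unknown correlation. Disagreement is common between 0.2 and 0.6 but rare at 0.7. Only half of it runs in the direction that reads as specific.
- **Spread.** Reduced spread in non-bvYOD is plausible, not established. The article states an expectation about level, not variance. The group is diagnostically mixed, and general cognitive decline could widen its scores.
- **General cognition.** A reader might infer that simple correlations leave the plan unable to account for general cognition, although the article says: "To account for the influence of other cognitive aspects, all general cognitive measures from Study 1 will also be administered in Study 2". The documents do not support that inference. Statistical analysis provides for confounders as covariates, and nothing rules out partial correlation. Covariates do not, however, supply a comparison between groups.

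It can also be said that a formal comparison has little power at 20 per group. That stands. It is a reason to report an interval, because the same data cannot support a confident verdict from separate tests either.

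**Conclusion.** The point holds. Aim 3 is a between-group question, and the article states only within-group correlations in groups of 20, judged by significance. Under identical relationships, two groups disagree on significance 23% to 49% of the time for true correlations of 0.2 to 0.6, and 8% at 0.7. At 0.5, the pattern that reads as specific occurs 23% of the time with equal spread, 37% if non-bvYOD has three-quarters of the SD and 50% at half. These figures rest on assumed correlations and SD ratios and on unadjusted alpha; they illustrate the problem and are not the exact operating characteristics of the plan. That a null in 20 people cannot show absence needs none of the assumed correlations or SD ratios.

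This should be fixed, but it does not threaten the study's main result. The Sample size section names the Study 1 difference between bvYOD patients and controls as the main outcome, and that analysis is untouched.

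**What to change.** 1. Test ecological validity with a pooled model without interaction on all 80 participants: risk-taking score on group, SC score and the plan's covariates. Report the common within-group slope with a 95% CI. This has roughly 80% power at a within-group correlation of about 0.31.
2. Judge generic or specific from a second model that adds SC × group. Report the slope differences for bvYOD v brain injury and bvYOD v non-bvYOD, unstandardised, with 95% CIs. Because several scores are bounded, name robust, bootstrap or rank-based versions for use if assumptions fail.
3. State that a non-significant correlation in one group of 20 will not be read as specificity, and that a non-significant slope difference will not be read as proof of a generic relationship.
4. Keep the group-wise correlations, with CIs, as description.

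The cost is analysis wording: no added participants or measures. Recruitment is planned to run to the end of 2026, so the change can be made before analysis. The downside is that the generic/specific answer will usually be a wide interval, since 20 v 20 detects only about r = 0.74 v 0.

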1)Assess sensitivity of new performance-based SC measures (including emotion experience and empathy) ◊ Study 12)Assess construct validity of the new performance based SC measures ◊ Study 13)Assess the relationship between social cognition and unsafe risk-taking behaviour (measuring ecological validity of the new SC tests), and investigate if this relationship is generic (by including patients with brain injury affecting frontal networks) or specific (by including patients with non-bvYOD variants, for whom no SC impairments or risk-taking behaviour are expected) ◊ Study 2

As a result of this study, we hope to introduce new, sensitive neuropsychological instruments which may aid in a more timely diagnosis of bvYOD and a better identification of social behavioural symptoms in general.

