### Sample size

The aim of the YOD-RiSoCo study is to aid in the diagnosis of YOD by improving measurement of social cognition. Therefore, the main outcome measure is the difference between bvYOD patients and healthy controls in performance on the new SC instruments. This way we hope to differentiate pathology in bvYOD from healthy controls and to prove the sensitivity of the instruments for the specific pathology.

The estimated effect size is based on a previous study assessing the sensitivity of a new social cognition task [27]. In this study, significant differences were found between patients and controls in performance on the SNQ-NL Total score, with a large effect size (η_p_^2^ = 0.23). However, considering that no studies have yet been conducted with the current measurements and in the current population, a moderate effect size of 0.5 (default option) for the power calculation was chosen.

The power calculation was performed with *G*Power 3.1* [28]. For achieving 80% power, with 20% chance for making a Type II error and a 5% significance, the estimated sample size per group is 64. If the required number of approximately 128 inclusions is still not achieved within 24 months, the inclusion period will be extended with 6 months. In case of missing data, we will include additional subjects to reach the target N.

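### Study 2 assesses specificity from a correlation in a group expected to show neither SC impairment nor risk-taking; at n=20 a null there cannot separate no relationship from little variation or low power

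*Protocol article*

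**What the plan says.** The aims at the end of the Background ask whether the link between SC and unsafe risk-taking is generic or specific. The specific arm is to be examined "by including patients with non-bvYOD variants, for whom no SC impairments or risk-taking behaviour are expected". The Abstract (Methods) explains specific as the relationship being absent in dementia without SC impairments.

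The Study 2 part of Statistical analysis fixes the method. SC tests and risk-taking measures are related "with parametric or non-parametric correlation analyses in the different groups (bvYOD, non-bvYOD, brain injury, healthy controls"), and a significant coefficient is taken to show an association. For the non-bvYOD group it then says: "for whom no SC impairments or risk-taking behaviour are expected, it will be assessed whether this relationship is specific".

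The design section for Study 2 "aims to include 20 patients with bvYOD, 20 healthy controls, 20 non-bvYOD patients and 20 patients with brain injury affecting frontal processes". The general rule for tests is that "the alpha will be set at 0.05, and analyses will be two-sided". The Sample size section covers the Study 1 group difference only.

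**The concern.** A correlation depends on the spread of both variables in the group where it is computed. A group chosen because it should be unimpaired on one variable and free of the behaviour on the other may have little spread in either. Several of the scores are bounded: the two ETIF subscales stop at 12, the ToM parts have maxima of 12, and the risk survey has 30 yes/no items. Crowding near the good end is therefore plausible. A rank correlation does not restore the lost spread.

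The closer the group comes to the plan's expectation, the less a null correlation says. The plan gives the group, the statistic, the significance criterion and the meaning of specific. Under that meaning, a null in non-bvYOD beside a significant result in bvYOD would count towards specificity, although the two underlying relationships could be identical.

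Generic versus specific is a named aim, and the Discussion links a Study 2 relationship to revising fitness-to-drive guidelines. It therefore matters to which patients the relationship is said to apply.

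**Working it through.** **The plan's own figure.** Sample size states that "a moderate effect size of 0.5 (default option) for the power calculation was chosen", and then "For achieving 80% power, with 20% chance for making a Type II error and a 5% significance", "the estimated sample size per group is 64". The normal approximation gives n = 2(1.960 + 0.842)²/0.5² = 62.8, so 63. The t-test calculation gives 63.77, so 64, with power 80.1%. The figure reproduces, but it says nothing about correlations at n=20.

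**What n=20 can detect.** With 18 degrees of freedom and two-sided 0.05, |r| must exceed 0.444. By Fisher's z, n = ((1.960 + 0.842)/atanh(r))² + 3. At r = 0.59 this is 20.1, so 80% power needs a true r of about 0.59. At r = 0.5 it is 29.0.

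**Effect of reduced spread.** Assume the same slope and residual SD in both groups. Let r be the correlation in bvYOD and u the SD of SC in non-bvYOD divided by that in bvYOD. Then

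r′ = r·u / √(1 − r² + r²u²).

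For r = 0.5 and u = 0.5: 0.25/√(0.75 + 0.0625) = 0.277.

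Power was simulated for the Pearson test at n=20 and two-sided 0.05. The chance of a significant result in bvYOD and a non-significant one in non-bvYOD is power(bvYOD) × (1 − power(non-bvYOD)). Power in bvYOD at r = 0.5 is 0.641.

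| u | r′ in non-bvYOD | Power there | Chance of the pattern, r = 0.5 |
|---|---|---|---|
| 1.3 | 0.60 | 84% | 0.641 × 0.165 = 0.106, about 10% |
| 1 | 0.50 | 64% | 0.641 × 0.359 = 23% |
| 0.75 | 0.40 | 43% | 37% |
| 0.5 | 0.28 | 22% | 0.641 × 0.780 = 50% |
| 0.33 | 0.19 | 12% | 56% |

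The row u = 1 is the part due to small samples alone. Reduced spread adds 14 points at u = 0.75 (37 − 23), 27 at 0.5 and 33 at 0.33.

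**Other values of r.** For u = 1, 0.75, 0.5 and 0.33 the pattern occurs in 14%, 32%, 55% and 69% of trials at r = 0.6, and in 4%, 17%, 46% and 70% at r = 0.7.

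**Does a slope comparison avoid this?** With unbounded, error-free scores, a test of equal unstandardised slopes rejects in about 5% of runs at every u. That does not carry over to scores at their limits. With identical latent slopes, non-bvYOD shifted 1.5 SD in the better direction and a floor on the risk measure, the slope test falsely rejected in about 8–19% of runs at r = 0.5 and 29–54% at r = 0.7, depending on the height of the floor. With an SC reliability of 70%, u = 0.5 and r = 0.7, it rejected in 13%.

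**Precision of a direct comparison.** As a rough guide, a Fisher z comparison of two correlations at 20 v 20 has standard error √(2/17) = 0.343. For 0.5 v 0 the ratio is 0.549/0.343 = 1.60, which gives power 36%. For 0.6 v 0 it is 52% and for 0.7 v 0 it is 72%.

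**The case against.** The strongest reply is that the decisive input is missing from the document. It gives no SD, reliability or expected correlation. It says only that impairment and risk-taking are not expected in non-bvYOD, and an unimpaired mean does not imply a smaller SD. These are dementia patients of mixed aetiology taking partly verbal, story-based tests, and they may vary widely. The bvYOD scores could instead be the compressed ones. This stands. It limits the size of the effect and leaves the direction intact if spread is reduced.

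A reader might infer that a finding of specificity is close to built in. The figures do not support that: at r = 0.5 the pattern appears in about half of trials even at u = 0.5, and at u = 0.75 with r = 0.7 in only 17%.

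A reader might also infer that the investigators will declare specificity from a null result. The article does not state that rule. It defines specific, makes significance the criterion for an association, and says that specificity will be assessed in this group. The risk is that the rule is left open to that reading.

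The article describes no comparison of mean risk-taking between groups. A condensed article may leave that to the full protocol, so its absence is not held against the plan. The commitments to check assumptions, use non-parametric alternatives and include covariates do not address spread.

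Finally, the main outcome is the Study 1 group difference, so this affects a secondary part of the project, though a named aim.

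**Conclusion.** The point holds as a weakness in a stated analysis. Using significance of a within-group correlation at n=20, in a group expected to show neither impairment nor the behaviour, does not answer the specificity question, because a null has at least three explanations that the analysis cannot separate.

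Under equal slopes and residual SD with r = 0.5, the misleading pattern ranges from about 10% (non-bvYOD more variable) through 23% (equal spread) to 56% (SD ratio 0.33). Both r and the SD ratio are assumptions. The calculation takes normal scores, one SC measure and one risk measure, and no multiplicity correction. Restriction of the risk measure itself, which would lower the correlation further, is not in the table.

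It would be tempting to conclude that slopes simply cure the problem. They remove the attenuation caused by a narrower SC range, but not the distortion from a ceiling, a floor or measurement error.

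**What to change.** In the Study 2 part of Statistical analysis:

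1. State that specificity will not be concluded from a significant correlation in bvYOD together with a non-significant one in non-bvYOD.
2. Base the specificity question on a direct between-group comparison of the SC-risk relationship: a group-by-SC interaction on unstandardised slopes, reported as an estimate with 95% CI. Show beside it each group's SD and the percentage at ceiling or floor on the SC and risk measures.
3. State that, where either measure is clearly at ceiling or floor in a group, specificity will be reported as not estimable, because the slope comparison is then biased too.

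A comparison of mean risk-taking between bvYOD and non-bvYOD would usefully check the stated expectation, but it is supporting material.

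The cost is some wording and one standard model on data already planned, with no extra participants. The downside is that the interval for the slope difference will be wide at 20 per group, so specificity may have to be reported as inconclusive.
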